### Statistical analysis

Two independent researchers will record all experimental data on CRF forms and enter them into the computer. Data will counted by statisticians using SPSS 19.0 statistical software. The mean ± standard deviation (M ± SD) will used for measurement data, paired sample tests will be used for before-and-after control within groups, independent sample tests will used for comparisons between groups, and chi-square tests will be used for efficacy grading. p < 0.05 is considered a statistically significant difference.

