### Outcome measures

#### Primary outcome

##### 5-HT and SP concentration

Serum 5-HT and SP concentrations in patients were determined before and after treatment using an enzyme-linked immunosorbent assay (ELISA). The level of 5-HT is closely related to the presence of diarrhea or constipation in irritable bowel syndrome, as well as SP [55, 56]. We will compare the efficacy of the two groups by ELISA of serum 5-HT and SP in patients before and after treatment.

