#### Statistical methods

##### Sample size

The test group sample size (massage with the probiotics group) and the control group (probiotics group) were randomly grouped in a 1:1 ratio, and the sample size was determined according to the bilateral hypothesis test, setting the test criterion as a = 0.05 (bilateral) and test efficacy as β = 0.20. The efficiency of the test group in the preexperimental observation is 90, and the efficiency of the control group is 60. The required sample was calculated to be approximately 60 cases, with an increase of 10% of cases taken off, and the actual sample size is approximately 66 cases; that is, 33 cases in the test group and 33 cases in the control group are selected.

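### The between-group tests on the continuous outcomes name no baseline adjustment although pretreatment values are collected, which costs power in a trial of about 30 per arm

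*Protocol article*

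**What the plan says.** The Statistical analysis section fixes three kinds of test. Within arms, "paired sample tests will be used for before-and-after control within groups". Between arms, and for the efficacy grade, "independent sample tests will used for comparisons between groups, and chi-square tests will be used for efficacy grading". It names no baseline covariate. It does not say whether the independent-sample test compares post-treatment values or changes, nor whether the chi-square test uses all the grades or a split into effective and ineffective.

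Baseline values will exist. The Abstract (Methods/design) has the results assessed before treatment, after treatment and at follow-up. For the biomarkers the outcome section says: "Serum 5-HT and SP concentrations in patients were determined before and after treatment using an enzyme-linked immunosorbent assay (ELISA".

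The Sample size section rests on a two-proportion comparison: "The efficiency of the test group in the preexperimental observation is 90, and the efficiency of the control group is 60", with "setting the test criterion as a = 0.05 (bilateral) and test efficacy as β = 0.20". It gives about 60 cases, raised to about 66. The section on evidence efficacy defines the grades as bands of percent improvement from the pretreatment score.

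**The concern.** 5-HT, substance P and IBS-SSS are the primary outcomes, IBS-QOL is secondary, and all are continuous with a pretreatment value. When baseline and follow-up are correlated, part of the follow-up variance can be predicted from the baseline. A test on post-treatment values leaves that part in the error term. A change score removes it only imperfectly and adds noise when the correlation is low. With about 30 evaluable patients per arm precision is short, and the adjustment needs no extra data. At stake is the chance of detecting a real effect of massage on the primary outcomes, and the width of the reported intervals.

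The same section leaves two smaller matters loose. The chi-square test on the grades is not tied to the two-proportion comparison on which the trial was sized. The within-arm tests share one significance threshold with the between-arm tests, and the text does not say which of them carry the efficacy conclusion.

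**Working it through.** **Inputs from the protocol article.** Two-sided alpha 0.05; beta 0.20, so power 0.80; effective rates 90 and 60, read as percentages; 1:1 allocation; about 60 required, 66 with 10% added (Sample size). Allowing for that 10% loss, 30 per arm is the relevant size.

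**Assumed, because the article gives no figure.** An effect of 0.6 SD; a baseline-to-follow-up correlation r of 0.3 to 0.7; equal variance at both times; and the grade distributions below.

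**1. The plan's own figure.** Arcsine formula: h = 2·asin(√0.9) − 2·asin(√0.6) = 0.726, and n = 2(1.960 + 0.842)²/h² = 29.8, so 30 per arm and 60 in total. The unpooled normal formula gives (1.960 + 0.842)²(0.9·0.1 + 0.6·0.4)/0.3² = 28.8, so 29 per arm and 58 in total. The stated 60 is reproduced, and 60 × 1.10 = 66. The figure belongs to a two-level comparison of effective rates.

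**2. Continuous outcomes.** Relative to a post-only test, the variance of the treatment difference is multiplied by 2(1 − r) for a change score and by 1 − r² for ANCOVA. Power comes from the noncentral t with noncentrality (d/√factor)·√(n/2), n = 30 and d = 0.6. Degrees of freedom are 58, or 57 for ANCOVA. For the post-only test the noncentrality is 0.6·√15 = 2.32 and power is 63%.

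| r | Change factor | Change-score power | ANCOVA factor | ANCOVA power |
|---|---|---|---|---|
| 0.3 | 1.40 | 49% | 0.91 | 67% |
| 0.5 | 1.00 | 63% | 0.75 | 75% |
| 0.6 | 0.80 | 72% | 0.64 | 81% |
| 0.7 | 0.60 | 84% | 0.51 | 89% |

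ANCOVA exceeds both alternatives at every r tried. At r = 0.3 the change score does worse than ignoring baseline. The effect detectable with 80% power is 0.74 SD post-only and 0.64 SD with ANCOVA at r = 0.5.

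**3. Efficacy grade.** Simulated power at 30 per arm, grades ordered best to worst, each pattern consistent with 90 versus 60:

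| Test arm vs control arm (%) | Four-level chi-square | Wilcoxon | Two-level test |
|---|---|---|---|
| 15/35/40/10 vs 5/20/35/40 | about 70% | 80% | 80% |
| 5/20/65/10 vs 5/20/35/40 | about 70% | about 37% | about 80% |

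In the first pattern the benefit is spread over the grades; in the second it only moves patients out of the lowest grade. With both arms at 5/20/35/40, the four-level chi-square rejects in about 4% of trials, so its type I error is sound despite sparse cells. The two-level test holds about 80% in both patterns because it depends only on the 90 versus 60 split.

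**The case against.** The strongest reply is that nothing here is invalid. Randomisation makes the unadjusted comparison unbiased, chance imbalance is already covered by its error rate, and every size above is assumed. A condensed article may also leave the choice of covariates to an analysis plan not shown. The first part stands, and the point is made only as one of efficiency. The last part carries less weight, because the article does name its between-group method and, as named, that method has no covariate.

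Three stronger readings are tempting and are not supported:

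- **That the plan uses t-tests that ignore baseline.** The text says only independent-sample tests and leaves open whether changes are compared. The efficacy grade itself is built on the pretreatment score. What can be said is that no adjustment is named, and that ANCOVA beats either reading.
- **That the chi-square test wastes power by ignoring the order of the grades.** The article does not say that four levels are tested. The 90 versus 60 sizing fits a two-level test, for which order is irrelevant. Even with four levels, the advantage of a Wilcoxon test reverses when benefit is confined to the lowest grade.
- **That the paired tests are offered as evidence for massage.** They are labelled as within-group and kept apart from the between-group comparisons.

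The document also gives no ground for requiring a log scale for 5-HT and substance P.

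**Conclusion.** The point holds for the continuous outcomes, as an avoidable loss of efficiency. At 30 per arm and 0.6 SD, ANCOVA gains about 4 to 26 percentage points over a post-only test (67% to 89% against 63%) and 18 to 5 points over a change score (67% against 49% at r = 0.3; 89% against 84% at r = 0.7). These sizes rest on the assumed effect, correlations and equal variances. The direction held at every correlation tried.

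For the grade, what remains is a need to state which comparison is meant and to tie it to the sizing; no general loss of power is shown. For the paired tests, what remains is to say that they are descriptive.

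**What to change.** In the Statistical analysis section:

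1. Analyse each continuous outcome by ANCOVA of the post-treatment value on arm and that outcome's own baseline value. Report the adjusted difference with its 95% CI.
2. Test the effective rate (effective versus ineffective) with the two-proportion test that matches the Sample size section, and state which grades count as effective.
3. Keep any ordinal analysis of the four grades secondary. It cannot be run until the section on evidence efficacy is reconciled: that section announces four levels but names three, and its range for ineffective (30% to under 95%) overlaps the two grades above it.
4. State that efficacy conclusions rest on the between-group comparisons and that the within-group paired tests are descriptive.

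The cost is wording only. No further patients or measurements are needed. The change should be fixed before the data are compared by arm.

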## Discussion

The complex and multifactorial nature of the pathogenesis of IBS means that single-drug treatments, such as probiotics, prebiotics, antimicrobials, anti-anxiety and antidepressant treatments and fecal transplants, are not as effective overall [56]. Complementary alternative medicine, including massage therapy, has been reported to be increasingly popular among clinicians and patients [57, 58].

Massage treatment has shown the advantages of safety, simplicity, economy, and nontoxic side effects. According to the study, one-finger meditation massage stimulates acupuncture points through gentle manipulation and thus exerts the therapeutic effect of the points. It is characterized by the continuous alternation of the force characteristics of the double waveforms during operation [59]. Using the fingers instead of acupuncture needles to stimulate the acupuncture points produces an effect similar to acupuncture, but compared to acupuncture, the one-finger acupressure technique has the advantages of noninvasiveness and safety. In our study, we focused on abdominal tui-na, using the technique to promote intestinal peristalsis on the one hand and selecting relevant acupuncture points to play the role of acupuncture points on the other hand.

Although massage treatment of irritable bowel syndrome has been proven effective, since IBS-C clinical research is still in its infancy, there are great shortcomings, and the number of clinical trials is very small, mostly relying on personal experience reports. Furthermore, there is a lack of evidence-based treatment and randomized controlled studies, poor credibility of the efficacy, and insufficient mechanism of research evidence to guide clinical practice. In our study, we conducted a randomized controlled study of massage treatment of IBS-C, which is the first of its kind in clinical practice, using the gut-brain axis as the theoretical basis. In addition to traditional abdominal tuina manipulation treatment, we combined traditional medicine acupressure therapy with the use of one-finger meditation therapy. The results of this study will continue to provide new ideas and methods for the treatment of irritable bowel syndrome-related conditions with massage. Ultimately, our hope is that the results of this trial will alleviate the symptoms of IBS-C patients, reduce their physical and psychological stress and improve their quality of life.

## Data Availability

This trial has been audited by the China Clinical Trials Registry and the experimental data will be shared on the Public Management Platform for Clinical Trials, the website is http://www.medresman.org.cn.
